### Program

The Behavioral Health Services division of the San Francisco Department of Public Health (SFDPH) has an extensive infrastructure for mental health and substance use disorder services, yet one important gap has remained: real-time response for people in behavioral health crisis in the streets. In 2019, San Francisco’s 9-1-1 call data indicates that approximately 50,000 behavioral health related calls were received, most of which were responded to by a law enforcement unit. Because most calls were not related to criminal events, and instead to mental health and social needs experienced by PEH, San Francisco behavioral health and governmental leaders worked with community stakeholders to create the SCRT to respond as an alternative able to be more responsive to behavioral health crises that happen on the street [16].

The SCRT was designed based on previous co-responder models [17, 18]. To meet the goal of diverting calls that would typically go to the San Francisco Police Department, this trauma-informed specialty behavioral health team is dispatched solely by 9-1-1 operators. The SCRT utilizes a co-responder model comprised of a behavioral health clinician, a paramedic from the San Francisco Fire Department and a peer specialist. Each team member plays a role in providing care including immediate stabilization of urgent medical need (paramedic), de-escalation of the crisis (behavioral health clinician) and person-centered peer support (peer specialist). The team triages clients to the appropriate level of care, be it through resolution of the crisis in the field, linkage to outpatient mental health and substance use services, or transport to an acute treatment setting. The SCRT was first piloted in San Francisco’s highest demand neighborhoods in December 2020 and then was incrementally expanded to be citywide by June 2021 (Fig 1).

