#### Study population

The SCRT aims to provide specialty mental health response and enhanced resources to adults in San Francisco who experience crises related to mental health and/or substance use disorders and are experiencing homelessness. Therefore, the study population will be defined based on age greater than 18 years, meeting criteria for homelessness in the 12 months prior to or 3 months following the crisis episode, and receipt of crisis care from any of San Francisco’s “front door” programs for people in an acute behavioral health crisis. These settings include two mobile crisis programs (Comprehensive Crisis Services and the SCRT), a crisis stabilization unit (DORE Urgent Care Clinic), and emergency psychiatric services (Zuckerberg San Francisco General Hospital’s Psychiatric Emergency Services [PES] and Emergency Department visits with a primary behavioral health diagnosis) (Fig 2). The population of housed adults utilizing acute behavioral health services will be utilized as a control group in the ITS sensitivity analyses.

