#### Interrupted time series analysis

The ITS analysis will examine three periods: 1) Pre-SCRT baseline (November 2019 to November 2020), 2) SCRT partial implementation (December 2020 to July 2021), and 3) SCRT full implementation (August 2021 to August 2022). Each of the outcome measures will be computed as a monthly proportion, with the numerator equaling the number of individuals meeting criteria for each outcome and the denominator equaling the total target population in a given month. Using month-long time intervals would yield between 8 and 12 data points per time period, though the final interval length may change depending on the trade-offs between length of observation and statistical power.

Generalized estimating equations (GEE) will be used, with robust standard errors to account for within-person correlation [27], to analyze the trends in outcomes pre-implementation, during partial implementation, and after the implementation of SCRT. Models will include a variable for time (month) after the beginning of our observation period, a variable for time each time period subsequent to baseline, and the interaction between these variables to assess change in the trajectory of each outcome. Models will be adjusted by the covariates described above and interaction terms constructed to understand the relative effects of covariates and the ITS variables.

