### Limitations

There are several limitations to the research methods described above. While ITS designs can measure the impact of a non-randomized intervention, this quasi-experimental approach may not yield definitive results and may be specific to San Francisco and therefore less generalizable to other regions. The electronic records used to describe health, housing and jail service utilization does not capture all services provided in settings outside of the San Francisco Department of Public Health. Though data from 9-1-1 dispatch might help identify which cases are being diverted from SFPD to the SCRT, these data will not be available for this evaluation. It is not possible to fully account for the potential impacts of COVID on data collection and service utilization. Incomplete data on the location of PEH may impede any location-specific analysis; in this case, only the pre-pilot and full implementation segments would be included in the ITS. Limitations in the semi-structured interviews may include sampling bias that results from recruitment through the clinical program, the difficulty of locating potential participants, and the need to exclude potential participants who do not have capacity to consent due to psychiatric or other symptoms; recall bias related to traumatic experiences while in crisis; and desirability bias due to difficulty describing negative experiences of the health care system.

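### SCRT is one of the entry points that define the study population, so the denominator changes as SCRT rolls out and each before/after change mixes residual case-mix change with program effect

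*Protocol article*

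**What the plan says.** The Study population section admits homeless adults who received crisis care from any front-door program. For the mobile services it states: "These settings include two mobile crisis programs (Comprehensive Crisis Services and the SCRT". The other doors are DORE, Psychiatric Emergency Services (PES), and emergency department (ED) visits with a primary behavioral health diagnosis.

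The Interrupted time series analysis section makes each of the four outcomes a monthly proportion, with "the denominator equaling the total target population in a given month". The first period is given as "Pre-SCRT baseline (November 2019 to November 2020". Partial implementation runs from December 2020 to July 2021, and full implementation from August 2021 to August 2022. The introduction to Quantitative methods reads the effect from the change in each outcome before and after implementation.

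The Program section reports that in 2019 "approximately 50,000 behavioral health related calls were received, most of which were responded to by a law enforcement unit". SCRT is dispatched only through 9-1-1. Its purpose is introduced with the words "To meet the goal of diverting calls that would typically go to the San Francisco Police Department", and it began in the "highest demand neighborhoods in December 2020 and then was incrementally expanded to be citywide by June 2021". The Limitations section concedes a gap in the data: "data from 9-1-1 dispatch might help identify which cases are being diverted from SFPD to the SCRT, these data will not be available". That section does not name the changing denominator as a threat.

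**The concern.** Every proportion is conditional on a recorded crisis episode, and the intervention creates such records. A person whose street crisis drew only a police response in 2019 had no route into the baseline denominator through that event. The same person met by SCRT in 2021 is in it. If such people differ from the others in routine care, reutilization, housing assessment or jail entry, the series moves although nobody's outcome has changed. The movement starts with the interruption and grows with the rollout, which is the pattern the model attributes to SCRT. It could look like benefit on one outcome and harm on another.

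**Working it through.** The protocol states no outcome rate, effect size or power figure bearing on this point, so there is no figure of its own to reproduce. Shares and rates below are assumptions; dates come from the protocol.

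**1. Timeline.** November 2019 to November 2020 is 13 months with no SCRT door. December 2020 to July 2021 is 8 months, and August 2021 to August 2022 is 13. The door opens in month 14, the first month of the second segment.

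**2. Formula.** Split a later month's index persons into (i) those who would have had an index episode that month through PES, the ED, DORE or Comprehensive Crisis Services anyway, and (ii) those who are counted only because SCRT exists. Only group (ii) changes the denominator. Let s be its share of index persons, pN its outcome rate, and pL the rate in group (i). With zero effect on anyone:

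- monthly proportion = (1 − s)·pL + s·pN
- crude shift = s·(pN − pL)

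**3. Numbers.** For s from 10% to 40% and gaps of 5 to 15 points, the smallest shift is 0.10 × 5 = 0.5 points and the largest is 0.40 × 15 = 6.0 points. Examples in percentage points:

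| Assumed rates, pL vs pN | s = 10% | 20% | 30% | 40% |
|---|---|---|---|---|
| Routine care, 40% vs 25% | −1.5 | −3.0 | −4.5 | −6.0 |
| Routine care, 40% vs 35% | −0.5 | −1.0 | −1.5 | −2.0 |
| Reutilization, 30% vs 20% | −1.0 | −2.0 | −3.0 | −4.0 |
| Jail entry, 10% vs 15% | +0.5 | +1.0 | +1.5 | +2.0 |
| Jail entry, 10% vs 7% (3-point gap) | −0.3 | −0.6 | −0.9 | −1.2 |

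The two jail rows show that the sign depends on rates nobody yet knows.

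**4. What the segmented model does with it.** A noiseless fit over 34 months used level and slope terms for each segment. The share s rose linearly over the 8 partial months and then stayed constant. For routine care at 40% vs 25% and s = 40%, the partial segment shows a level change of −0.75 and a slope of −0.75 points per month. The full segment shows a level change of −6.0 and no slope. At s = 10% the corresponding figures are −0.19, −0.19 and −1.5. The whole composition shift falls on the implementation terms.

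**5. Would it be detected as an effect?** Take 300 legacy index persons per month (assumed) and a crude 13-month pre/post comparison at two-sided 0.05, treating observations as independent. The 40% vs 25% case is significant with probability 0.29, 0.82, 0.99 and 1.00 for s = 10% to 40%. At 100 per month the probabilities are 0.12, 0.38, 0.73 and 0.94. People recur across months, so these are rough indications only.

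**6. The plan's safeguards against this mechanism.**

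- Pilot versus non-pilot zip codes: new entrants appear where and when SCRT is active, so the influx follows exposure.
- Housed control group: SCRT is aimed at homeless adults, so the influx need not be equal in the two groups and need not cancel.
- Non-equivalent outcomes: the example given, non-crisis initiation of outpatient care, does not depend on entry through a crisis episode.
- Covariates: they remove the shift only as far as recorded variables capture the difference.
- Entry-point trajectory variable: SCRT entry does not exist at baseline, so adjusting for it cannot separate case mix from effect.

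**7. Why a refit on constant entry points is not a bound.** Take 100 legacy users, 50 with a routine-care rate of 50% and 50 with 30%, so the mean is 40%. With zero true effect, suppose SCRT diverts 20 of the first group and adds 20 new people at 25%.

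- Legacy doors only: (30 × 0.50 + 50 × 0.30) / 80 = 30/80 = 37.5%.
- All doors: (40 + 20 × 0.25) / 120 = 45/120 = 37.5%.

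Both fits fall by 2.5 points and agree, yet there is no effect.

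**The case against.** The strongest reply is that the plan already adjusts for what is likely to differ: crisis, routine care, jail and housing encounters in the prior 12 months, diagnosis, involuntary hold, suicidality and violence risk. It also builds the entry-point variable, allows covariate interactions with the time-series terms, and admits that diverted cases cannot be identified. This stands in part. Adjustment should shrink the shift, so the figures above are pre-adjustment and only the residual matters.

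Several stronger readings are tempting, and the documents do not support them:

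- *The baseline holds only facility crises.* Comprehensive Crisis Services is a mobile team and already an entry point, so the contrast is one of degree.
- *People met by police left no record.* The Program section says of calls, not persons, "most of which were responded to by a law enforcement unit". It does not say how many callers then reached PES or the ED.
- *All SCRT users are new to the denominator.* Index episodes are one per person per month, and some SCRT users would have been counted through another door. SCRT's share of episodes is therefore the wrong multiplier.
- *The series would jump in December 2020.* Rollout was incremental and has its own segment, so the shift would build up gradually.

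It can also be said that a condensed article may leave a restricted sensitivity analysis to a fuller plan. That is fair, and the point does not rest on that absence. It rests on the population and denominator that the article does fix.

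**Conclusion.** The point holds in a limited form. The intervention adds people to the denominator of its own outcomes, starting at the interruption, and the comparisons described do not reliably cancel this. An unadjusted shift of 0.5 to 6 points with zero true effect is plausible under the assumed shares (10-40%) and gaps (5-15 points). The actual SCRT-only share, the gap, the sign, and the amount left after adjustment cannot be derived from the protocol. A reader might infer that the series cannot inform on SCRT at all, or that the bias favors the program; neither follows. What follows is that a change in a monthly proportion cannot, by itself, be reported as an effect of SCRT on the people served.

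**What to change.** - **(a)** Report and model monthly index persons by entry point as their own interrupted series beside each outcome, with baseline covariates by entry point.
- **(b)** As a sensitivity analysis, refit the four outcome models on the entry points open in all three periods: PES, ED, DORE and Comprehensive Crisis Services. State that diversion of legacy users into SCRT can bias this fit too. Do not treat agreement between the two fits as proof of effect, or the pair as bounds.
- **(c)** Where data allow, add a secondary analysis whose denominator needs no crisis contact, such as jail entries and PES/ED crisis visits per 1,000 persons flagged as homeless before the month. Exclude flags that arise only from SCRT contact or its follow-up, because homelessness status is itself recorded through service contact.
- **(d)** Name the changing denominator in the limitations and limit the effectiveness conclusion accordingly.

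Items (a) and (b) need a few extra models on data already being linked. Item (c) needs a monthly count of flagged persons and covers only some of the outcomes. The main cost is that results may have to be called inconclusive where the analyses differ.

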**Fig 2 pone.0295178.g002:**
[figure not shown]
System map of crisis system entry points in San Francisco used for defining index crisis episodes. MC–mobile crisis; CF–crisis facility; ED–emergency department; SCRT–Street Crisis Response Team; CCS–Comprehensive Crisis Services (adult/child mobile crisis team in San Francisco); DUCC–DORE Urgent Care Center; ZSFG ED–Zuckerberg San Francisco General Hospital Emergency Department; PES–Psychiatric Emergency Services. ‡—ZSFG ED limited to medical episodes with primary ICD-10 diagnosis of mental health, substance use, or suicide Z-codes.

#### Data sources and matching procedures

The primary data sources for our quantitative analysis will include electronic health record (EHR) data from the network of clinics funded by the city’s health plan, public housing assessment data, and jail entry data. We will integrate data from SFDPH’s two main EHR vendors, Avatar (NetSmart) and EPIC, which are used by SFDPH mental health and substance use treatment providers, medical clinics, mobile crisis teams, crisis stabilization units, and Zuckerberg San Francisco General Hospital’s medical ED, psychiatric emergency services (PES) and inpatient psychiatry. Homelessness and housing assessment data originate from the Homeless Management Information System (HMIS), which is used by all entry points into the housing service system in San Francisco and automatically links data into the EPIC EHR. Jail entry data originates from the Jail Information Management System (JIMS), which the Department of Public Health’s Jail Health Services clinicians use to assess every person who enters the San Francisco County Jail, as well as Epic following their transition to this EHR in October 2021.

We will use a two-step process for linking records from the Avatar, Epic (including HMIS) and JIMS EHRs by first matching on demographic data fields such as first and last name, date of birth, legal sex, and at least one additional element (e.g., Social Security Number (SSN), full street address, phone number, or email address), and then an additional round of name matching using a Jaro-Winkler based process with matching parameter = 1 (i.e., exact match) [20, 21]. Unique individuals and episodes will be assigned anonymized identifiers to create a limited dataset that includes information about demographics, clinical attributes, dates of service, and zip codes. Authors did not have access to personal health information or other personal data that could identify individuals during or after data collection for the ITS.

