#### Index crisis episode

Conducting an ITS that includes a time-dependent outcome—in this case a routine care episode, acute care episode, housing assessment, or jail entry within 30 days following a crisis episode—requires defining an index crisis episode to start the clock for the outcome time interval. Furthermore, given that there may be multiple index episodes per unique individual, the index crisis episode needs to be defined per ITS interval, which, based on our preliminary power analysis, will be divided as one calendar month per interval. The index crisis episode will therefore be defined as the first instance in a given month that an individual has a crisis episode, with the 30-day post-crisis outcome period trailing the end date of the index episode.

We also need to account for the fact that a single crisis episode may result in multiple contacts with different settings in the acute behavioral health care system. To account for this variability, we will use our clinical knowledge of common care pathways as the basis for a crisis system map (Fig 2) that defines different sequences of care as either a step-up in service intensity (e.g., mobile crisis followed by crisis stabilization or ED), a step-down in service intensity (e.g., PES followed by crisis stabilization), or a distinct crisis episode that mostly likely signifies reutilization (e.g., PES followed by mobile crisis, or two consecutive mobile crisis episodes). We will then combine sequences with a step up or down in service intensity that occur within two or fewer days between the end of the first and start of the second clinical setting, so as not to miscount these care transitions as reutilization. This approach also allows us to create a variable describing these crisis system trajectories, thus allowing us to identify potential differences between index crisis episodes based on crisis system entry point and end point. All crisis services utilized three or more days after the index crisis episode end date will be considered separate from the index crisis episode.

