#### Outcome variables

We will build ITS models using the following four repeated measures outcomes: 1) post-crisis episode routine care utilization within 30 days; 2) post-crisis episode crisis service reutilization within 30 days; 3) post-crisis episode housing assessment within 30 days; and 4) post-crisis episode jail entry within 30 days. Routine care services will include receipt of outpatient services within 30-days following the index crisis episode in programs related to mental health, substance use, primary care, and integrated behavioral health in primary care. We will exclude residential programs and other services that are not intended to serve as routine care nor as a front-door crisis service. Acute care reutilization will include when an individual has a crisis care episode within 30-days following discharge from the index crisis episode. Housing assessment will be determined among those who are identified as PEH as having an HMIS record of receiving a housing assessment within 30-days following the index crisis episode. Finally, we will measure jail entry within 30-days following the index crisis episode based on clinical records from JIMS or Epic that are documented for every person who enters the San Francisco County Jail.

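### The jail-entry data source changes two months into the full-implementation period, and neither the stated model nor the limitations account for it

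*Protocol article*

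**What the plan says.** Under Data sources and matching procedures, the protocol article names JIMS as the origin of jail data, "as well as Epic following their transition to this EHR in October 2021". Outcome variables defines a single pooled outcome, "based on clinical records from JIMS or Epic that are documented for every person who enters the San Francisco County Jail".

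Records from Avatar, Epic and JIMS are joined by "first matching on demographic data fields such as first and last name, date of birth, legal sex, and at least one additional element", followed by a further round of exact name matching.

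Interrupted time series analysis sets three segments: "Pre-SCRT baseline (November 2019 to November 2020"), "SCRT partial implementation (December 2020 to July 2021") and "SCRT full implementation (August 2021 to August 2022"). The model terms it names are calendar time, the later periods and their interactions, plus patient covariates. No term represents the source of the jail record.

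The same section lists design safeguards: a pilot versus non-pilot comparison in the partial phase, a comparison with housed crisis users, and outcomes that the programme should not affect. Study population places the housed comparison among the sensitivity analyses. Limitations mentions possible COVID effects on data collection but not the change of jail record system.

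**The concern.** An interrupted time series attributes to the programme any shift that coincides with its breakpoint. A change in how the outcome is recorded or linked, close to the breakpoint, is the standard instrumentation threat. Here it falls inside the full-implementation segment, near its start.

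A complete jail log does not settle the matter. The outcome also requires that a jail record be attached to the right person's crisis episode. Before the switch that attachment relied on matching JIMS to other systems. Afterwards the jail record sits in Epic, alongside part of the health record. The proportion attached could therefore rise or fall with no change in true jail entry. If it rose, the programme would look as though it increased jail entry, or a true fall would be hidden. If it fell, the programme would be credited with a reduction. Jail entry is one of the four main outcomes, and the Discussion names diversion from jail as something the study is meant to explain.

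**Working it through.** **Inputs.** Segment dates come from Interrupted time series analysis, the switch month from Data sources and matching procedures, and the 30-day window from Index crisis episode. The article gives no jail-entry rate, match rate, link function or monthly counts. The check therefore uses a linear model on the proportion scale with equally weighted months, no covariates and no autocorrelation, and an abrupt shift of size D percentage points at the switch. D is unknown.

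**Calendar count.** November 2019 to November 2020 is 13 months, December 2020 to July 2021 is 8, and August 2021 to August 2022 is 13, giving 34 in total. The article says "Using month-long time intervals would yield between 8 and 12 data points per time period". The exact count is 13, 8 and 13, so that range is one month short at the top. This does not affect the point. The switch comes 2 months after the August 2021 breakpoint, leaving 11 of 34 months after it.

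**Overlap of the two steps.** All 11 post-switch months lie in the full-implementation segment, 2 months are full implementation before the switch, and 21 are neither. The correlation is (11 × 21) / √(13 × 21 × 11 × 23) = 231 / 262.8 = 0.88.

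**September 2021 is partly exposed.** The outcome is measured "with the 30-day post-crisis outcome period trailing the end date of the index episode". An episode ending on day d of September has d of its 30 follow-up days in October. If end dates are spread evenly, the average is 15.5 / 30, or about one half. The check is therefore run twice: with a clean October step, and with September coded 0.5 (correlation then 0.92).

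**Bias if the switch is not modelled.** The full-implementation segment has its own level and slope, so the artefact is absorbed by a straight line fitted to its 13 months, k = 0 (August 2021) to 12, with mean 6 and Σ(k − 6)² = 182.

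- Clean step (k = 2 to 12 exposed): mean exposure 11/13 = 0.846; slope 11/182 = 0.060; level at August 0.846 − 6 × 0.060 = 0.48.
- Half step in September: mean exposure 11.5/13 = 0.885; slope (11 − 2.5)/182 = 0.047; level at August 0.885 − 6 × 0.047 = 0.60.

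| Per 1 point of D | Clean step | Half step |
|---|---|---|
| Average full-implementation effect | 0.85 | 0.88 |
| August 2021 level change | 0.48 | 0.60 |
| Slope change, per month | 0.060 | 0.047 |
| December 2020 level and slope | 0 | 0 |

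Dropping the partial phase, the fallback in Limitations, leaves the full-implementation biases the same. For illustration only, an assumed D of 1 to 3 points in either direction biases the average effect by about 0.85 to 2.7 points in that direction.

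**Cost of modelling the switch.** A source step is added to the design matrix, and each standard error is compared as √([(X₂ᵀX₂)⁻¹]ⱼⱼ / [(XᵀX)⁻¹]ⱼⱼ), where X₂ includes the step. The August 2021 level change rises by 7 to 12% (clean) or 16 to 27% (half step), depending on how the periods are coded. The slope change rises by 5 to 15%, and the average effect by 13% or 20%. The source term itself has a variance inflation factor of 7.2 or 10.8, so its own estimate will be imprecise.

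**The case against.** **Separability.** A reader might infer from the correlation of 0.88 that the switch and the programme effect cannot be told apart. That does not follow. Under the stated segmented model a source step is estimable with moderate loss of precision. What remains true is that the level change would then rest on two pre-switch months, only one of them clear of the 30-day overlap, and on linear trends.

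**Scope.** A reader might also infer that every jail result is affected. The December 2020 terms carry no bias, and the pilot versus non-pilot comparison belongs to a phase that ends in July 2021, before the switch. Only the full-implementation contrast is exposed.

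**Mechanism and direction.** It is tempting to say that people experiencing homelessness lack the extra identifiers, so linkage must improve in Epic. The article does not say that they lack them. It does not say whether the name round is an added requirement or a second chance to match. It does not say which system holds which index episodes, and any held in Avatar still need cross-system matching after October 2021. It also describes the jail records as covering everyone who enters. Neither a change in capture nor its direction is established.

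**Existing protection.** Housed crisis users pass through the same switch, so the planned comparison with them removes a common artefact. This stands, with two limits: it is a sensitivity analysis, and it leaves any part that differs by housing status.

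**Condensed article.** Source indicators and match-rate tables are often left to a fuller plan. That is fair as to detail. However, the article itself states the switch date, the pooled outcome, the model terms, a list of validity safeguards and the limitations, and none of the last three addresses the switch.

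**Conclusion.** The point holds as an unaddressed instrumentation risk confined to the full-implementation effect on jail entry. If capture or linkage changed at October 2021, the model as described would read about 85 to 88% of the change as the average full-implementation effect, and about 48 to 60% as the August 2021 level change. These fractions assume equal monthly weights, an abrupt switch, a linear scale and a slope change in each period, as the article's interaction terms imply. With level changes and one common trend only, the fraction entering the full-implementation effect would be 28 to 45%.

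The size of the artefact is not given and may be zero. The documents do not support saying that the jail result is wrong, that it is biased upwards, or that the housed comparison must become the main analysis. The risk still merits a planned check, because the exposed contrast concerns a main outcome and the check is cheap.

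**What to change.** For the jail outcome:

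- Add a sensitivity model with a data-source step at October 2021, coding September 2021 index episodes as partly exposed, by the share of each 30-day window that falls after the switch. Report the full-implementation terms with and without the step. Do not read a non-significant source term as evidence of no artefact, since that term is imprecise.
- Report jail-record match rates by month, source and housing status. The split by housing status shows whether the comparison with housed adults can be relied on to cancel the artefact.
- Optionally, as a check only, apply the same demographic matching rule to the Epic jail records as to JIMS. This gives up some true matches after the switch, so it should not replace the main linkage.
- Name the switch under Limitations and when interpreting the full-implementation jail effect.

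Ending the series at September 2021 is not a useful substitute: it leaves two full-implementation months, one of them already overlapping the switch.

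The cost is one extra model, one table and, if chosen, one linkage re-run. In the extra model the standard errors of the full-implementation terms rise by roughly 5 to 27%.
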